### Access to a Peer Recruitment Toolset

The primary element of the peer recruitment toolset is our Facebook website plugin [20,26,27]. The Facebook plugin will allow smokers to browse through their Facebook friends and recruit them by sending private recruitment messages. In our pilot study [20,26,27], providing smokers access to peer recruitment quadrupled our sample (190 smokers recruited 569 more smokers to the Decide2Quit DISC). Further, the smokers recruited by their peers were more likely to be African American as compared to those who were directly recruited from an online social network (23.8% vs 10.8%; *P*<.01 for all comparisons). Thus, in our dissemination hypothesis, we are testing if providing smokers access to peer recruitment specifically increases the proportion of African Americans in our sample.

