**Figure 1 figure1:**
[figure not shown]
Flow of participant randomization. Allocation to receive the peer recruitment tools occurs in two phases or waves. Wave 1: Half of the enrolled smokers are randomized to receive peer recruitment tools, while the others do not receive the tools; and Wave 2: All subsequent smokers who are randomized to the effectiveness trial and also report they were peer-recruited are given access to the peer-recruitment tools.

The basic flow of a single hypothetical smoker through the peer-referral, registration, and subsequent initiation of new peer-recruitment is described in Figure 1. Peer recruitment will take place in waves. As is common in peer recruitment approaches, to initiate the waves, we will recruit the first wave (wave 0 or seeds) of smokers. Seeds will be recruited using online advertisements. Once a seed registers on Decide2Quit and receives the peer recruitment toolset, we expect the following to occur:

The seed consents to be in the study and recruit smokers from his/her network using the peer-recruitment tools (by sending a Facebook private message).The successfully peer-recruited smoker (wave 1 recruit) registers on the system and consents to recruit other smokers in his/her social network.The wave 1 recruit then continues the peer-recruitment chain, recruiting smokers his/her their social network.The successfully peer-recruited smoker then registers (wave 2 recruit). The waves progress until the target sample size is reached.

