### Study Design

As noted in Figure 1, all participants registering online on the Decide2Quit DISC will first undergo an effectiveness randomization and then a peer recruitment allocation. The effectiveness randomization will randomly assign participants to either receive access to the recommender system CTHC or the standard CTHC. The peer recruitment allocation will depend on the recruitment source. As noted in the section below, we will either directly recruit participants to the study (via search engine advertisements and research match) or they will be recruited by their peers (peer recruited). Directly recruited peers will be randomized to either receive the peer recruitment toolset or not receive the toolset. All peer recruited participants will receive access to the peer recruitment toolset. We are using this approach for the peer recruited smokers to enhance blinding. This decision was made because these recruited smokers may communicate with their peers about the intervention.

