### Sample Size

#### Hypothesis 1: Dissemination

Our previous work [26,27] showed that having access to peer recruitment increased the proportion of African Americans to 23%, compared to 11% in the initial seeds (those recruited by advertisements). Using 10% as the base rate in the nonpeer recruitment group (no access to peer recruitment), we estimated sample size requirements by varying the proportion in the peer recruitment from 16% to 20%. With these assumptions, for our primary aim, we will need 219 smokers in each group to detect a difference of 10% (power=80%, α=.05). If we reduce the difference to 8% and 6%, we will need 319 and 525 participants in each group, respectively. Given that we will work with our panel to encourage recruitment of African American smokers in the peer recruitment group and may see bigger differences than those in our pilot study, we will have adequate power, particularly with the proposed sample size of 600 in each recruitment method. For recruitment time, previous trials estimated that the mean number of days to recruit a sample of 700 smokers was 244 (SD 81) days [27,40]. Assuming that peer recruitment proceeds with the same rate and SD, we can detect a difference in recruitment time as low as 14 days. Since we expect the comparison rate to be much slower, we are adequately powered to detect differences with a sample of 600 (power=80%).

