To test Hypothesis 3 (effectiveness), we will compare participants randomized to enhanced CTHC and those randomized to standard CTHC. We will use the 7-day point prevalence cessation of the 6-month follow-up as the dependent variable in generalized linear models. Using mediation analysis, we will examine the potential mechanisms through which we anticipate the intervention to produce a beneficial effect. We will categorize the NicAlert test into smokers and nonsmokers’ categories and use the Chi-square statistic to test for differences. If risk reduction (decreased number of cigarettes smoked) is normally distributed, we will use the identity link function in the generalized linear model. We will also model risk reduction using count regression with a Poisson or negative binomial regression modeling if the variance of the distribution of risk reduction is over dispersed. For Hypotheses 2 and 3, we will compare African American smokers across the groups, and African American and white smokers for heterogeneity.

To assess the difference in smokers comparing the peer recruitment and standard recruitment, we will use a three-step strategy. First, we will collect data on covariates (minority status, education, readiness to quit, and income) that have been shown to differ between the peer recruitment and standard recruitment [26]. We will use these variables to adjust our overall models with the outcome of smoking cessation, comparing participants from peer recruitment and those from standard recruitment. Second, peer recruitment is, in many ways, analogous to clustering. Each person who is recruited by another individual is clustered in the group of the initial peer recruiter. Thus, some component of the difference is within the relationship between recruiter and recruitee. To address this issue, we included a marker for each “recruiter” as a fixed effect in the model. Third, we will use an advanced approach, termed complier-averaged causal effect analysis (CACE), to compare those who complied (peer recruited or not) in the intervention group with those who would have complied in the comparison group if they had been exposed to the intervention (peer recruitment). Thus, after adjustment using the first and second approach, we will conduct additional models using CACE.

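### Step 2 of the supplementary peer-versus-standard cessation comparison uses recruiter fixed effects, which remove the contrast or narrow it to a different one

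*Protocol article*

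**What the plan says.** The protocol article, under Statistical Analyses, sets out a three-step strategy for differences between recruitment routes.

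- Step 1 adjusts models of smoking cessation for covariates, "comparing participants from peer recruitment and those from standard recruitment".
- Step 2 deals with clustering. The article states: "Each person who is recruited by another individual is clustered in the group of the initial peer recruiter". The remedy is that the authors "included a marker for each “recruiter” as a fixed effect in the model".
- Step 3 is a complier-average causal effect (CACE) analysis: "after adjustment using the first and second approach, we will conduct additional models using CACE".

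Other sections show who can have a recruiter. The text under Figure 1 says: "Seeds will be recruited using online advertisements". Study Design separates direct recruits (search advertisements and ResearchMatch) from peer recruits, and adds: "All peer recruited participants will receive access to the peer recruitment toolset".

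The article does not say whether a recruiter carries the same marker as his or her recruits. It also uses a second definition of the groups. The sample size text for Hypothesis 1 defines the comparison group by toolset access: "Using 10% as the base rate in the nonpeer recruitment group (no access to peer recruitment".

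**The concern.** Recruiter is nested in recruitment route: a peer recruit has a recruiter and a direct recruit does not. A fixed effect for each level of a nested factor absorbs all the between-group information, and that information is the comparison the model is meant to deliver.

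Statistical software usually drops a redundant column rather than stopping. A coefficient labelled as the peer effect could then be printed whose value depends on which recruiter became the reference. If the coding happens to avoid exact redundancy, the printed coefficient answers a different and narrower question. In either case a reader would take it for the cluster-adjusted effect of recruitment route. The Discussion says the difficulty of measuring cessation by recruitment type has been dealt with in the analysis plan, and step 2 is the part of that answer that handles clustering.

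**Working it through.** **Inputs.** The group contrast, the cluster definition and the fixed-effect marker come from Statistical Analyses. Cessation rates of 15% and 24% come from the sample size text for Hypothesis 3. The article gives no figure for this comparison, so there is none to reproduce.

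**1. Plain reading.** Let P = 1 for a peer recruit and 0 for a direct recruit. Let M_j = 1 if the participant was recruited by, or in the chain of, recruiter j. Each peer recruit has exactly one M_j equal to 1, and each direct recruit has none, so Σ_j M_j = P for everyone. The model is

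logit(p) = a + bP + Σ_j g_j M_j + covariates.

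Replace b by b + c and every g_j by g_j − c. Every fitted value is unchanged for any c, so b is not identified. This needs no assumed counts, and the step 1 covariates do not cure it.

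**2. Other codings.** The rank of [intercept, markers, group indicator] was checked on an invented data set: 300 direct recruits without the toolset, 300 seeds with it, and 560 peer recruits of 172 recruiters, 1,160 people in all. The counts are assumptions (60% of seeds recruit, about 3.3 recruits each). With 172 recruiters, 300 − 172 = 128 seeds recruit nobody.

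| Group indicator | Who carries a marker | Columns | Rank | Who informs the contrast |
|---|---|---|---|---|
| Peer recruited | Recruits only | 174 | 173 | Nobody: not estimable |
| Peer recruited | Recruits and their seed | 174 | 174 | 560 recruits and their 172 seeds; 0 of the other 428 direct recruits |
| Toolset access | Recruits only | 174 | 174 | 600 direct recruits; 0 of 560 peer recruits |
| Toolset access | Recruits and their seed | 174 | 174 | 300 without toolset and 128 non-recruiting seeds; 0 of 560 peer recruits |
| Toolset access | Every seed and its chain | 302 | 301 | Nobody: not estimable |

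The second row compares recruits with their own seed, and 428 of 600 direct recruits (71%) drop out. The third and fourth rows compare seeds with direct recruits who lack the toolset, and every peer recruit drops out. In the fourth row 560 + 172 = 732 of 1,160 people (63%) are unused. If covariates are added, those left out inform only the covariate coefficients. None of the five codings estimates the overall comparison of recruitment routes.

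**3. Binary outcome in small clusters.** For a cluster of m people with independent outcomes and quit rate q, P(all identical) = q^m + (1 − q)^m.

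- m = 2: 0.15² + 0.85² = 0.745; 0.24² + 0.76² = 0.635.
- m = 3: 0.15³ + 0.85³ = 0.618; 0.24³ + 0.76³ = 0.453.
- m = 4: 0.523 and 0.337.
- m = 1: always 1.

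In a logistic model the effect of such a cluster diverges, and the cluster gives no within-cluster information.

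**4. Reach of the problem.** Hypothesis 1 uses a chi-square test and a t test. Hypothesis 2 uses a generalized linear model with two indicators and their interaction. Hypothesis 3 compares CTHC groups randomized participant by participant, so CTHC can vary within a recruiter's group. Step 1 has no markers. None of these becomes inestimable.

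**The case against.** The best defence is that the article leaves the coding open. Step 2 is motivated by the tie between recruiter and recruit, which suggests that the two share a marker; the matrix then has full rank and a coefficient exists. The group indicator may also mean toolset access, as in the sample size text for Hypothesis 1, and then full rank is again possible. This stands: a reader might infer that the effect can never be computed, and the text does not support that. It does not rescue step 2, because the full-rank codings estimate something other than the comparison named in the same paragraph. Reading the marker as a single yes/no flag would also avoid the redundancy, but would not represent the clustering described.

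Three further limits stand.

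- A reader might conclude that the trial's main results are at risk. Cessation by recruitment route is not among Hypotheses 1 to 3, and the randomized comparison is unaffected.
- A reader might turn the pilot figure, "190 smokers recruited 569 more smokers to the Decide2Quit DISC", into about three recruits per recruiter (569/190 = 2.99) and conclude that about half the clusters are uninformative. That ratio is best read as recruits per smoker given access. How many of the 190 recruited anyone is not stated, and clustering by initial recruiter could give larger groups.
- A reader might assume that the CACE models fail too. The article says only that they follow steps 1 and 2, not that they keep the markers.

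**Conclusion.** The point holds in a limited form. Recruiter fixed effects are the wrong device for a between-route contrast. On the plain reading the effect is not identified, which is exact algebra and rests on no assumed numbers. On the other codings examined it is either unidentified again or replaced by a narrower contrast. The extent of that narrowing (71% of direct recruits unused under one coding, all peer recruits under two others) depends on the invented counts or coding and is illustrative. The identical-outcome percentages assume independence and fixed cluster sizes; positive correlation within clusters would raise them.

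The damage is confined to step 2 of a supplementary analysis and to any CACE model that retains the markers. It should be fixed, but it does not threaten a hypothesis-level result. This is a rule the article states, not a detail it leaves to a fuller document.

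**What to change.** In step 2, drop the recruiter fixed effects and use one of the following:

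- a logistic model with a random intercept for recruitment chain, the chain being defined by its root seed; or
- GEE logistic regression with robust standard errors clustered on root seed.

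Place each root seed in the same cluster as all its descendants, treat each direct recruit without descendants as a cluster of one, and keep the peer-versus-direct indicator as the estimand. State that definition of the indicator explicitly, since the article elsewhere defines the groups by toolset access. Say whether the CACE models carry any recruiter term and, if so, use the same chain-level handling there.

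The cost is a sentence or two in the analysis plan. The recruiter-to-recruit links are already needed for the planned markers, so no new data are required. Preliminary analysis is reported as under way, so the change should be recorded before this comparison is run or reported. It handles the clustering only: recruitment route is still not randomized, and the step 1 covariate adjustment is still needed.

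### Read literally, the CACE step defines compliance by recruitment source, which is not randomised, so it has no randomised instrument; it should be limited to direct recruits, with toolset allocation as the instrument

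*Protocol article*

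**What the plan says.** Statistical Analyses sets out three steps for studying cessation by recruitment type, "comparing participants from peer recruitment and those from standard recruitment". Step one adjusts for minority status, income, schooling and readiness to quit, covariates described as "shown to differ between the peer recruitment and standard recruitment". Step two adds a fixed effect for each recruiter. Step three, run after that adjustment, is CACE. On the intervention side it takes "those who complied (peer recruited or not) in the intervention group". Their counterparts on the other side are described as "those who would have complied in the comparison group if they had been exposed to the intervention (peer recruitment".

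Study Design says how people reach these groups. Participants either come in directly, through advertisements or ResearchMatch, "or they will be recruited by their peers (peer recruited". It then states: "The peer recruitment allocation will depend on the recruitment source". For direct entrants: "Directly recruited peers will be randomized to either receive the peer recruitment toolset or not receive the toolset". For the others: "All peer recruited participants will receive access to the peer recruitment toolset". The legend of Figure 1 describes the same allocation.

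**The concern.** CACE takes its causal force from a randomised offer (the instrument) and a behaviour that follows the offer (compliance). In this design the behaviour named as compliance comes before registration and decides the allocation, so the usual order is reversed. A direct recruit who is given the toolset cannot later become peer recruited, and recruitment source itself is never assigned at random.

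The risk is that a difference in who arrives by each route is reported under a label that readers take to mean a causal effect. The protocol itself expects the sources to differ on characteristics that plausibly predict quitting. The Discussion says that the challenge of comparing cessation by recruitment type has been dealt with in the analysis plan. The CACE step as written does not add that protection.

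**Working it through.** The protocol gives no figure for the CACE, so there is nothing to reproduce. The check is whether the estimator identifies what it claims to.

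**Inputs.** Total sample 1200 (Study Overview). Quit rate in direct recruits 15%, borrowed from the control rate in Sample Size, Hypothesis 3. Allocation as in Study Design. Assumptions: a 1:1 split of direct recruits; 60, 300 or 600 peer recruits; quit rates of 10%, 15% or 20% in peer recruits.

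**Literal reading.** Let Z = 1 for the toolset group and D = 1 for peer recruited. Peer recruits all have Z = 1, so P(D=1|Z=0) = 0. Let π be the peer-recruited share of the toolset group, qp and qd the quit rates in peer recruits and in direct recruits without the toolset, and τ the toolset effect in direct recruits.

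- Toolset group: E[Y|Z=1] = π·qp + (1 − π)(qd + τ)
- No-toolset group: E[Y|Z=0] = qd
- Wald CACE = (E[Y|Z=1] − E[Y|Z=0]) / π = (qp − qd) + τ(1 − π)/π

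With τ = 0 this is exactly qp − qd, the non-randomised contrast between sources, whatever the value of π.

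**Numbers.** With 300 peer recruits there are 900 direct recruits, 450 per arm, so the toolset group is 450 + 300 = 750 and π = 300/750 = 0.40. With qp = 20%, the toolset group quits at (450 × 0.15 + 300 × 0.20)/750 = 0.17. Then (0.17 − 0.15)/0.40 = 0.05.

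Simulation of 4,000 trials per scenario, with no true effect of the toolset or of peer recruitment, agrees. With 300 peer recruits the mean estimate is −5.0, 0.0 and +5.0 points for qp of 10%, 15% and 20%. It stays near those values for 60 to 720 peer recruits. The randomised contrast among direct recruits alone stays at 0.0.

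These figures are unadjusted. After steps one and two, qp − qd is replaced by whatever difference between sources the adjustment leaves.

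**Alternative reading.** Suppose the parenthesis means that the participant did or did not recruit peers, and let c be the share of the toolset group who did. The numerator is still π(qp − qd) + (1 − π)τ, because the toolset group still contains peer recruits. With τ = 0, π = 0.40 and qp − qd = 5 points, the numerator is 2 points. At an assumed c of 50% the estimate is 2/0.50 = 4 points, and at 25% it is 8 points, again from selection alone.

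**Share of the toolset group not randomised (1200 in total)**

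| Peer recruits (assumed) | Direct recruits per arm | Toolset group | Not randomised |
|---|---|---|---|
| 60 | 570 | 630 | 9.5% |
| 300 | 450 | 750 | 40% |
| 600 | 300 | 900 | 67% |

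**The case against.** The strongest defence is that the sentence speaks of compliance within an intervention group. If the intervention is toolset access and compliance is recruiting peers, this is close to a conventional CACE. Some sections do use the term peer recruitment for access to the toolset: Sample Size, Hypothesis 1 describes the comparison group as having no such access. So the wording is ambiguous. However, Study Design uses peer recruited for a route of entry, and the strategy's stated contrast is between sources. The defence also fails on its own terms, because nothing limits the analysis to the randomised direct recruits.

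Four stronger readings are tempting, and the protocol does not support them.

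- **That nothing about peer recruitment was randomised.** Toolset access is randomised among direct recruits. Only recruitment source is not.
- **That the fault is the absence of compliers in the comparison group.** Compliers are latent in the control arm of any CACE with one-sided non-compliance. The fault is the missing randomised instrument.
- **That the result carries all the selection of an unadjusted comparison.** CACE follows the adjustment in steps one and two. What it lacks is any protection beyond that.
- **That most of the toolset group must be non-randomised, by carrying over the pilot's yield of 569 recruits from 190 smokers.** The Recruitment section makes direct recruitment the primary method and says only that peer recruits may occur. Sample Size plans 600 per recruitment method. The share is unknown in advance.

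It is also fair to say that these are additional models, tied to none of the three hypotheses, and that an article may leave estimator detail to the analysis plan. That would excuse silence. Here the compliance variable and the contrast are stated, and they do not fit the design.

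**Conclusion.** The point stands. On the literal reading, the CACE has no randomised instrument and reduces to the quit-rate difference between sources when the toolset has no effect, less whatever the adjustment removes. On the alternative reading, it is still compromised by pooling non-randomised peer recruits with randomised direct recruits.

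The identification argument needs only the allocation rules in Study Design. The size rests on assumptions: a 5-point difference between sources gives a 5-point spurious effect on the literal reading, and 10% to 67% of the toolset group is non-randomised for 60 to 600 peer recruits. The direction of any bias is not known.

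The correction is worth making, but the main results do not depend on it. The comparison of recommender with standard CTHC is randomised for everyone and is unaffected.

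**What to change.** 1. Limit the CACE to directly recruited participants, with randomised toolset allocation as the instrument.
2. Define compliance as an action after allocation among those given the toolset, for example contacting or recruiting at least one peer. Table 1 lists peers recruited and friends or family contacted among the 1-month measures. Plugin records could serve if they are kept, but the protocol does not say that messages are logged.
3. Estimate the CACE as the intent-to-treat difference in 6-month cessation divided by the proportion complying.
4. State the exclusion restriction: having the toolset without using it does not change a participant's own cessation. This needs a defence, since Hypothesis 2B expects toolset access to raise repeated use of the website.
5. State the estimand as the effect of toolset use on the user's own cessation.
6. Report peer recruited versus directly recruited cessation, with the adjustment of steps one and two, as an observational association and not as CACE.

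**Cost.** Mostly wording, plus confirmation that the compliance measure is available for toolset users. The question becomes narrower, because it no longer concerns the effect of being peer recruited. Precision falls. With 450 direct recruits per arm and 15% cessation, the intent-to-treat standard error is √(2 × 0.15 × 0.85/450) = 0.024, so the CACE standard error is about 0.024/0.50 = 4.8 points at an assumed 50% compliance. With 300 per arm it is √(2 × 0.15 × 0.85/300)/0.50 = 5.8 points. Lower compliance widens it in proportion.
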